### Sample size

Although there are limited studies to base a statistical power calculation, the sample size was determined based on previous sample size estimates from trials using sub-symptom threshold aerobic exercise (STAE) interventions, which ranged from 46 to 96 participants [20, 21]. With an estimated drop-out rate of 20%, we will aim to recruit 120 participants [21].

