### Compliance to the intervention

Participants will be withdrawn from the study if there is a change in medications or if they are unable to attend follow-ups. Self-reported compliance to the intervention will be tracked at weekly follow-up visits via REDCap survey. Fitbit data can also verify adherence to exercise protocol and will be quantified via the following formula [61]:$$\mathrm{A}\mathrm{d}\mathrm{h}\mathrm{e}\mathrm{r}\mathrm{a}\mathrm{n}\mathrm{c}\mathrm{e}=\frac{{(\mathrm{v}\mathrm{o}\mathrm{l}\mathrm{u}\mathrm{m}\mathrm{e})}_{\mathrm{a}\mathrm{c}\mathrm{t}\mathrm{u}\mathrm{a}\mathrm{l}}}{{(\mathrm{v}\mathrm{o}\mathrm{l}\mathrm{u}\mathrm{m}\mathrm{e})}_{\mathrm{p}\mathrm{r}\mathrm{e}\mathrm{s}\mathrm{c}\mathrm{r}\mathrm{i}\mathrm{b}\mathrm{e}\mathrm{d}}}\times 100$$$$=\frac{{(\mathrm{H}\mathrm{R}\times \mathrm{t}\mathrm{i}\mathrm{m}\mathrm{e}\times \mathrm{f}\mathrm{r}\mathrm{e}\mathrm{q}\mathrm{u}\mathrm{e}\mathrm{n}\mathrm{c}\mathrm{y})}_{\mathrm{a}\mathrm{c}\mathrm{t}\mathrm{u}\mathrm{a}\mathrm{l}}}{{(\mathrm{T}\mathrm{a}\mathrm{r}\mathrm{g}\mathrm{e}\mathrm{t}\mathrm{H}\mathrm{R}\times 20\times 1)}_{\mathrm{p}\mathrm{r}\mathrm{e}\mathrm{s}\mathrm{c}\mathrm{r}\mathrm{i}\mathrm{b}\mathrm{e}\mathrm{d}}}\times 100$$

The numerator represents the volume of exercise performed divided by the volume of exercise prescribed to the participant. Volume actual is determined by multiplying weekly mean HR recorded during home exercise by weekly mean exercise time in minutes by the number of days per week out of 6 completed (i.e. 3 out of 6 days completed = 3/6 = 0.5). Volume prescribed was determined by multiplying weekly target HR by 20 min by days prescribed (every day excluding scheduled visit = 6/6 = 1). Participants who had an adherence rate of 66.67% or more were adherent, whereas participants with a rate lower than 66.67% were considered to be nonadherent [61].

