### Attrition and adherence

To ensure attrition and program adherence, participants’ HR will be collected using a Fitbit Versa 3 and monitored using Fitabase (Small Steps Labs, LLC) [62], a software that synchronises and displays Fitbit data in real-time. If it is observed that a participant’s HR does not reach within the prescribed range, a member of the research team will check in via text or email. Participants will also be required to complete a written diary given at each follow-up to document the type of exercise they completed, how long they exercised for, and if any PPCS symptoms were triggered by engaging in exercise. Additionally, participants will be offered a $50 e-gift voucher at baseline and at each follow-up to encourage attendance. Participants will be withdrawn if they are unable to complete daily exercise or attend follow-ups.

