### Data analysis

Primary and secondary outcomes will be assessed between groups at the primary endpoint (week 4) using two-sample *t*-tests (if normally distributed) or Mann-Whitney *U* tests (if not normally distributed). In addition, variables with multiple time points will also be assessed using generalised linear mixed-effects models. Models will be adjusted for confounders such as age, sex, baseline depression/anxiety/stress, history of migraine or other comorbidities, and cardiovascular fitness (Godin assessment). Feasibility (recruitment, retention, and completion rates), adherence (proportion), and safety (number and types of adverse events) will also be assessed. A statistician will be consulted in the events of missing data, any additional analysis, and to advise on interim analyses and stopping guidelines. Participants who do not complete the full 4-week intervention (i.e. lost to follow-ups) will be excluded from the primary endpoint analysis however will be retained in the descriptive analyses of the feasibility outcomes. Only the principal investigator will have the authority to terminate the trial.

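### The primary week-4 comparison leaves out women who do not finish the programme, so it conditions on an event after randomisation and is open to selection bias in either direction

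*Protocol article*

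**What the plan says.** The Data analysis section compares the arms at week 4 with a two-sample t-test, or a Mann-Whitney test if the data are not normal. It then restricts that comparison: "Participants who do not complete the full 4-week intervention (i.e. lost to follow-ups) will be excluded from the primary endpoint analysis". These women "will be retained in the descriptive analyses of the feasibility outcomes". On longitudinal data it adds: "In addition, variables with multiple time points will also be assessed using generalised linear mixed-effects models". On gaps in the data it says: "A statistician will be consulted in the events of missing data".

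Two other sections decide who stops being followed. Compliance to the intervention states: "Participants will be withdrawn from the study if there is a change in medications or if they are unable to attend follow-ups". Attrition and adherence states: "Participants will be withdrawn if they are unable to complete daily exercise or attend follow-ups".

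The Sample size section gives the expected loss: "With an estimated drop-out rate of 20%, we will aim to recruit 120 participants". The Design section describes an open-label superiority trial of effectiveness. Table 2 schedules the PCL-5 at baseline and on days 7, 14, 21 and 28.

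**The concern.** Randomisation makes the two arms comparable as allocated. It does not make the women who finish one programme comparable with those who finish the other. Finishing is decided after allocation, in an unblinded trial, under two programmes that ask different things: a heart-rate target in one arm, and gentle stretching that should not raise heart rate much in the other.

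The withdrawal rules make this more than passive loss. A medication change may follow worsening symptoms, and so may an inability to keep up the daily programme. The two sections list different triggers, and neither says whether the PCL-5 is still collected afterwards. If it is not, the rules themselves create the missing week-4 scores that the analysis then leaves out.

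At stake is the primary conclusion. If women who are doing badly leave one arm more often than the other, the remaining groups differ even when the programmes have the same effect. The trial could then report a benefit that is not there, or miss one that is.

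**Working it through.** **Step 1: the plan's own figure.** The Sample size section cites earlier trials with 46 to 96 participants and a 20% drop-out rate. Taking the upper end, 96 / (1 − 0.20) = 120, which reproduces the target. Expected exclusions are 120 × 0.20 = 24, leaving 96, or about 48 per arm. The article gives no SD, effect size or arm-specific drop-out, so everything below rests on assumptions.

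**Step 2: size of the bias.** Assume 60 randomised per arm, no true effect and a week-4 score with SD 1 (higher is worse). In each arm a share d drops out, through a latent variable that has correlation ρ with the week-4 score. The mean of those who remain is shifted by −ρ × m(d), where m(d) = φ(z) / (1 − d), z = Φ⁻¹(1 − d), and φ and Φ are the standard normal density and distribution function.

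m(10%) = 0.1950; m(15%) = 0.2743; m(20%) = 0.3500; m(25%) = 0.4237; m(30%) = 0.4967.

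The bias is the shift in the exercise arm minus the shift in the stretching arm. Type I error comes from simulation (20,000 replicates, two-sided 5% t-test on the women who remain).

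| Drop-out, exercise vs stretching | ρ | Bias (SD) | Type I error |
|---|---|---|---|
| 20% vs 20% | same in both arms | 0 | 5% |
| 25% vs 15% | 0.3 to 0.5, both arms | −0.3 × 0.1494 = −0.045 to −0.5 × 0.1494 = −0.075 | 5.5% to 6.6% |
| 30% vs 10% | 0.3 to 0.5, both arms | −0.3 × 0.3017 = −0.09 to −0.5 × 0.3017 = −0.15 | 7% to 12% |
| 20% vs 20% | 0.5, exercise only | −0.5 × 0.3500 = −0.18 | 14% |
| 30% vs 10% | 0.5, exercise only | −0.5 × 0.4967 = −0.25 | 23% |

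A negative sign favours exercise. Swapping the arms reverses the sign and leaves the type I error the same.

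**Step 3: cross-check by a second route.** Suppose non-completers end D worse than completers in the same arm. The size of the bias is then d(exercise) × D(exercise) − d(stretching) × D(stretching). With D between 0.5 and 1.0 SD in both arms, and a normal approximation for the type I error:

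- 25% vs 15%: 0.10 × D = 0.05 to 0.10 SD, type I error 5.7% to 7.8%.
- 30% vs 10%: 0.20 × D = 0.10 to 0.20 SD, 7.7% to 16.3%.
- 20% in both arms, with only the exercise leavers worse: 0.20 × D = 0.10 to 0.20 SD, 7.8% to 16.5%.

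The two routes agree in order of size.

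**Step 4: in PCL-5 points.** With an assumed SD of 12 to 18 points, 0.05 SD is 0.6 to 0.9 points and 0.25 SD is 3.0 to 4.5 points.

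**Step 5: would the weekly scores help?** In one illustration drop-out depended on the observed week-2 score (30% vs 10%; assumed week-2 to week-4 correlation 0.7). The bias among completers was −0.14 SD. Using the week-2 score reduced it to about 0.01 SD. That holds when drop-out is explained by observed scores. In Step 2 drop-out depends on the week-4 score itself, and there a model on the earlier scores removes only part of the bias.

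**The case against.** The best defence is the bracket. Equating non-completion with loss to follow-up can be read as limiting the exclusion to women with no week-4 visit, and they could not enter a week-4 t-test under any rule. This reading is fair, but the result is still a complete-case analysis, and the withdrawal rules still feed it.

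Second, a mixed model is already planned, and weekly PCL-5 falls within its scope. A reader might infer that a woman who leaves after week 2 contributes to no efficacy analysis at all. The article does not say that: the exclusion is worded for the primary endpoint analysis only. What remains is that the model is additional and that its population is not given.

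Third, differential drop-out is not established. The article gives one overall rate. It screens out women unwilling or unable to exercise, sets an individual target for exercise-intolerant women, and uses the same session length, weekly visits and vouchers in both arms. A reader might infer that the bias will favour exercise. The documents do not support that, since disappointed controls could leave too.

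A reader might also infer that women below the 66.67% adherence threshold are excluded. The article only classifies them as nonadherent.

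The promise to consult a statistician about missing data does not restore women whom the same paragraph removes. Nor is this a detail left to the SAP: the article fixes the rule, and an SAP that analysed everyone would contradict it.

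**Conclusion.** The point holds. The stated primary analysis compares groups defined by an event after randomisation, and at the planned drop-out it leaves out about one woman in five. This does not show that the result will be biased, or in which direction. The bias is zero if drop-out acts identically in both arms or is unrelated to outcome within each arm. In the assumed scenarios of Step 2 it runs from about 0.05 to 0.25 SD, with a type I error of about 5.5% to 23%. The upper figures need drop-out related to outcome in one arm only, and the milder 25% vs 15% split stays below 7%. Because the rule governs the primary conclusion of a superiority trial, and data collection is expected to run to May 2027, it should be changed before analysis.

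**What to change.** Replace the exclusion sentence with wording of this kind: *The primary analysis includes all randomised participants in the arm to which they were allocated. It is a likelihood-based mixed model with baseline and every available PCL-5 score from weeks 1 to 4 as responses. The week-4 difference between arms is the primary contrast.* This promotes a model the article already plans. Having baseline among the responses means that women who leave before week 1 still contribute.

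Report the completers comparison as supportive. Add one missing-not-at-random sensitivity analysis, for example delta-adjusted, because the model deals only with drop-out explained by observed scores.

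Reconcile Compliance to the intervention, Attrition and adherence, and Data analysis, so that stopping the intervention is separated from stopping outcome collection. Keep collecting the scheduled PCL-5 where the participant agrees. When the intervention itself should stop is a clinical matter on which this point takes no position.

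The cost is a wording amendment, some continued PCL-5 collection after the intervention stops, and an estimate that may be less favourable than the one among completers.

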### Ethics and dissemination

This study has been approved by the Monash University Human Research Ethics Committee (#40295) and registered with the Australian New Zealand Clinical Trials Registry (ID: ACTRN12624000893505). Results from this trial will be disseminated in published articles in peer-reviewed journals as well as in presentations at local and international conferences. Participants will be able to access all published, de-identified data in journal publications. A lay summary of overall study findings, along with the abstract of any publications, can be communicated if they wish via email or post.

## Discussion

Women with a history of IPV are at a high risk of PTSD. While there are trials investigating the effectiveness of yoga and psychomotor therapy in reducing PTSD symptom burden [63–65], to our knowledge there are no clinical trials exploring the effectiveness of aerobic exercise in patient cohorts specific to women who have experienced IPV. The primary aim of this study is to explore the effectiveness of a 4-week aerobic exercise intervention compared to a stretching intervention in relieving PTSD symptom burden in women with a history of IPV. Moreover, this research will determine the impact of aerobic exercise on other common comorbid mental health conditions (i.e. depression and anxiety) as well as cognitive functioning post-intervention. Lastly, weekly blood collections will help uncover potential objective biomarkers for PTSD and evaluate physiological responses to exercise in this population. Results of this trial will inform future approaches in constructing individualised, financially accessible, and self-directed treatment plans for women experiencing long-term mental and physical health challenges due to IPV.

### Trial status

The current protocol is v5, dated 12/05/2025. Recruitment for this study began on 16/05/2024. At the time of submission, we are currently recruiting and enrolling participants in the study. Data collection is expected to be completed on 16/05/2027.

## Data Availability

Not applicable.

## Abbreviations

ASSIST-lite: Alcohol, Smoking, and Substance Involvement Screen Test—lite
BCBT: Buffalo Concussion Bike Test
BDNF: Brain-derived neurotrophic factor
BPI: Brief Pain Inventory
DASS-21: Depression, Anxiety, and Stress Scale—21 items
DS: Digit Span
ECG: Electrocardiogram
HR: Heart rate
IL: Interleukin
IPV: Intimate partner violence
ITQ: Internal Trauma Questionnaire
O-SDMT: Oral Symbol Digit Modalities Test
PAR-Q: Physical Activity Readiness Questionnaire
PCL-5: Post-Traumatic Stress Disorder Checklist for DSM-5
PPCS: Persisting post-concussion symptoms
PTSD: Post-traumatic stress disorder
RAVLT: Rey Auditory Verbal Learning Test
REDCap: Research Electronic Data Capture
RPE: Borg Ratings of Perceived Exertion
RPM: Revolutions per minute
RPQ: Rivermead Post-Concussion Symptom Questionnaire
SF-12: 12-Item Short Form Survey
SRI: Sleep Related Impairment
STAE: Sub-symptom threshold aerobic exercise
TMT: Trail Making Test
TOPF: Test of Premorbid Functioning
VEGF: Vascular endothelial growth factor
WHOQOL-BREF: World Health Organisation Quality of Life—abbreviated
